### Markers of immunodevelopment

Early life immune system development follows a standardized trajectory recently described in human infants [2]. By analyzing ~ 50 markers per immune cell we are able to assess all white blood cell populations and their phenotypic and activation state. By mapping the immune development in this proposed study, we can directly compare immune developmental trajectories between children with different microbiomes.

### Markers of allergens and vaccine responses

The secondary outcomes are the differences in markers of allergy and vaccine responses at 12 and 24 months of age.

### Power analysis

The trial is designed with a planned sample of 100 mothers, allowing the final number of the subjects with an estimated 40% drop-out rate due to screening positivity to be 60 (30 in each intervention group) taking into consideration that it is likely to have drop-outs during the follow-up period.

Heterogeneity of microbiota is calculated as an index and used as the primary outcome at 3 months of age. The Standard Benjamini–Hochberg corrections for multiple testing are applied when testing multiple taxa. FDR-corrected *p*-values < 0.15 are considered statistically significant, but if needed uncorrected *p*-values are reported for clarity. 15 infants per CS group would be sufficient to detect a moderate effect size of 0.25 standard deviations for our primary outcome (power calculation for balanced one-way ANOVA test, 85% power, α = 0.05).

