**Fecal screening**
* Salmonella, Shigella, Campylobacter, Yersinia enterocolitica/pseudotuberculosis,* Enterohemorragic *E. coli* (EHEC), Enteroaggregative *E. coli* (EAEC), Enteroinvasive *E. coli* (EIEC), Enterotoxigenic *E. coli* (ETEC), Enteropatogenic *E. coli* (EPEC), *Clostridium difficile*, Parasites, Noro virus, Multi drug resistant gram negative bacteria (MDRGN), Vancomycin Resistant *Enterococcus* (VRE), *Listeria monocytogenes, Helicobacter pylori*, Sars-CoV-2

The eligible women are randomized into placebo (*GP*, 30 women), and intervention group *(GI*, 30 women). The randomization 1:1 is done in blocks of 4 mothers. The study is double blinded. The laboratory technicians who prepare the FMT product also perform the computer-generated randomization.

For promoting the study, we have set up posters and informed the staff at the maternity clinics, and used social media.

A fecal sample of 100 g and a blood sample of 15 mL are collected from the mother approximately two weeks prior to scheduled CS for screening of contagious diseases (Fig. 1). The mother divides the feces into the administered sample tubes according to written instructions. Feces for the transplant is collected into an empty tube using a spoon in the cap. The mother informs the research nurse, who delivers the tubes taken for screening to the laboratory as soon as possible, where the transplant is prepared from the fresh sample – this process is completed with a 6 h time frame.

The fresh fecal sample is screened for the presence of parasites and pathogenic viruses and bacteria (Fig. 1, Table 1). An aliquot (0.125 g) of the fresh fecal sample is used to determine the bacterial composition of the sample. Another part of this fresh sample is used as the transplant and for that purpose 1 g of feces is dissolved in 15 mL of isotonic saline and 10% glycerol, homogenized, and the 0.5 mL aliquots of the transplant are immediately frozen and stored at -80 °C [32].

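### The claimed 85% power with 15 infants per group for a 0.25 SD effect is about 10%, or 26% if 0.25 means Cohen's f; at the planned 30 per arm it is 16% or 48%

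*Protocol article*

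**What the plan says.** The Power analysis section of the protocol article makes a heterogeneity index at 3 months the primary outcome and gives one power statement for it: "15 infants per CS group would be sufficient to detect a moderate effect size of 0.25 standard deviations for our primary outcome". The method follows in brackets: "power calculation for balanced one-way ANOVA test, 85% power, α = 0.05".

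The same section plans for 100 mothers, with "an estimated 40% drop-out rate due to screening positivity", which brings the final number "to be 60 (30 in each intervention group"). It expects further losses during follow-up but gives no rate for them. The Study design text describes two arms, placebo and intervention, and says "The randomization 1:1 is done in blocks of 4 mothers". No SD, covariate, repeated-measures correlation or number of ANOVA groups is given that would change the calculation.

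**The concern.** A comparison of two groups of 15 is small, and 0.25 SD is a small difference between two means. High power for that combination is implausible on its face. The word "moderate" and the reference to ANOVA suggest that 0.25 may be Cohen's f, for which 0.25 is the conventional medium value. For two groups, however, f = 0.25 is a difference of 0.5 SD, not 0.25 SD, and 15 per group still looks far too few.

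This is the only power stated for the primary outcome. A reader who trusts it could take a null 3-month result as ruling out small or moderate effects of the transplant. The statement that 15 are enough also makes the loss of up to half of each arm look harmless.

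**Working it through.** **Inputs.** From Power analysis: n = 15 per group, effect 0.25, balanced one-way ANOVA, α = 0.05, target power 85%, planned 30 per arm. From Study design: k = 2 arms, 1:1.

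**Formula.** Power = P(F′ > F_crit), where F′ is noncentral F with k − 1 and k(n − 1) degrees of freedom and noncentrality λ = k·n·f². For two groups f = d/2, where d is the difference in SD units, and the F test equals the two-sided t test.

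**Attempt to reproduce the plan's 85%** (k = 2, n = 15, df = 1 and 28, F_crit = 4.196):
- 0.25 as a difference in SD: f = 0.125, λ = 30 × 0.015625 = 0.469, power **10.1%**.
- 0.25 as Cohen's f (d = 0.5): λ = 30 × 0.0625 = 1.875, power **26.2%**.

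Neither comes near 85%.

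**Other settings tried at n = 15**
- One-sided test, two groups: 16.4% (d = 0.25) or 37.9% (f = 0.25).
- α = 0.15, two groups: 23.9% (d = 0.25) or 46.5% (f = 0.25).
- More groups with f = 0.25: 28.5% for k = 3, 38.2% for k = 6, and only 72.1% for k = 20.

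**Power and detectable difference by number analysed** (k = 2, two-sided α = 0.05). The protocol article gives no follow-up loss rate, so 25 and 20 per arm are assumed values.

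| Analysed per arm | Power, d = 0.25 | Power, f = 0.25 (d = 0.5) | Difference detectable with 85% power |
|---|---|---|---|
| 15 | 10.1% | 26.2% | 1.13 SD |
| 20 | 12.0% | 33.8% | 0.97 SD |
| 25 | 13.9% | 41.0% | 0.86 SD |
| 30 | 15.9% | 47.8% | 0.79 SD |

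**Size needed for 85% power:** 289 per arm for d = 0.25, or 73 per arm for f = 0.25. With three groups and f = 0.25 it is 60 per group.

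**Where could 15 come from?**
- If 0.25 is η², the share of variance explained, then f = √(0.25/0.75) = 0.577 and λ = 30 × 0.3333 = 10. Power is 86.3% with 15 per group and 83.7% with 14, so 15 is the smallest number that reaches 85%. The implied difference is d = 2 × 0.577 = 1.15 SD, which is 1.15/0.25 = 4.6 times the effect stated.
- If 0.25 is f² (f = 0.5) with three groups, power at 15 is 83.4%; 16 per group are needed, giving 86.0%.
- If 0.25 is the between-group variance with five groups, power at 15 is 86.7%, but nothing in the text supports five groups.

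**The case against.** The strongest defence is that the calculation was sound and only the label is wrong. The number of ANOVA groups is not stated. The phrase "15 infants per CS group would be sufficient" and the article's interest in vaginally delivered infants leave room for a third, reference group. Under η² = 0.25 with two groups, or nearly so under f² = 0.25 with three, 15 per group is about right. The cause therefore cannot be identified with certainty. Under each of these readings, though, the description as 0.25 standard deviations is still wrong, and the η² and f² readings are large effects on the usual scale, not moderate ones.

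It can also be said that an ANOVA effect called moderate is most naturally Cohen's f, so that 26% and 48% are fairer figures than 10% and 16%. That is reasonable. It changes the size of the gap and does not close it.

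Third, the true effect may be large: the earlier series described in the Background reports that the microbiota of seven treated infants no longer resembled that of untreated cesarean-born infants. The article gives no standardised effect from that series, so it cannot support the stated power. Nor does the article say that a null result will be read as no effect; that harm is a risk, not a stated plan.

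Finally, the Microbiome outcome section compares the groups on beta-diversity by PERMANOVA. The figures here apply to a single index analysed by ANOVA, as the power statement assumes, and do not carry over to PERMANOVA. That limits their scope but does not rescue the sentence, which rests its claim on ANOVA.

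**Conclusion.** The stated effect, sample size and power are mutually inconsistent. Against a claimed 85%, power with 15 per group is 10% for 0.25 SD or 26% for f = 0.25. With all 30 per arm it is 16% or 48%, so even a true 0.5 SD difference would be missed slightly more often than found. On a single index, the trial has 85% power for about 0.79 SD at full size and about 1.13 SD if only 15 per arm remain.

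This rests on two groups, a scalar outcome with equal variances, and two-sided α = 0.05. One-sided testing, α = 0.15 or a third group does not restore 85% for either reading of the stated effect. The error needs correcting because it is the only justification of sample size for the primary outcome.

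**What to change.** Replace the power sentence. State the effect measure, its value, the number of groups and the outcome to which the calculation applies. Suggested text: *With 30 infants analysed per arm, a two-group comparison of the primary index at two-sided α = 0.05 has 85% power for a difference of 0.79 SD; with 25 or 20 per arm, taken as illustrative follow-up losses, the detectable difference is 0.86 or 0.97 SD.*

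Delete the description of the effect as moderate and as 0.25 standard deviations. If variance explained was meant, say η² = 0.25 and add that for two groups this is about 1.15 SD. If a third group was assumed, say so and give its size and source. Make clear that these figures are for the scalar index and not for the PERMANOVA.

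The cost is wording only. Randomisation, the planned 30 per arm and the analysis stay as they are; what changes is that the stated sensitivity becomes less favourable.

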## Data Availability

Findings from this study will be communicated with the scientific community and participants. Scientific communication will be through presentations at relevant international and domestic conferences and meetings, as well as publications in peer-reviewed journals.

## Abbreviations

CRP: C-reactive Protein
CS: Cesarean section
FMT: Fecal microbiota transplant
FUT2: Fucosyltransferase 2
GBS: Group B *streptococci*
GI: Intervention group
GP: Placebo group
VD: Vaginally-delivered
